### Longitudinal behavioral and compliance data

We will collect both quantitative and qualitative behavioral data and cookstove use compliance data monthly during the study periods. Compliance with improved cookstove use will be assessed by asking women how many total meals were cooked per day in the household in the preceding two weeks and how many were cooked using the new cookstove. We will ask how often a cookstove was used for a purpose other than cooking, what proportion of those times the cookstove was used, and what types of fuel sources were used. We will also determine if the intervention cookstove was not used during its corresponding intervention period and the reasons for the decision. Any modifications to the new cookstoves made by the families and any damage or breakdown of the cookstove will also be recorded during these monthly visits. We will also ask about length of cooking time to better understand whether the new stoves alter cooking time, which could be important for understanding compliance and acceptance.

In addition to the structured survey data on compliance and practices, we will use semi-structured interviewing techniques to assess individual preference and attitudes toward cookstoves and ways in which participants have adapted existing cooking practices and stove-use practices. Longitudinal qualitative interviews will provide an opportunity to assess how individual attitudes towards cookstoves, and ultimately acceptance of the new technology, are shaped over time and with repeated use. We will also assess changes in cooking practices over time. At the end of the trial, we will ask participants to indicate their preferred cookstove and to complete a final in-depth interview regarding individual preference, experiences using all three cookstove varieties, and the perceived benefits and drawbacks of each stove.

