## Methods

### Study objectives

This study is a multi-country, feasibility intervention trial of improved, ventilated cookstoves to inform a future, large-scale field trial. We aim to characterize environmental, health and respiratory outcomes in three diverse resource-limited settings (Kenya, Nepal and Peru) with the goal of providing a more robust understanding of the improved cookstove adoption process and factors related to sustained use of improved, ventilated cookstoves. We will install two different types of improved cookstoves with a chimney, in rural households where biomass fuels are used almost exclusively for cooking, and evaluate the intervention based on the following specific aims:

1. Compare particulate matter (PM) and CO concentrations between traditional cookstoves (before intervention) and two types of improved cookstoves with a chimney (after intervention).

2. Compare respiratory outcomes (spirometry, PEF, exhaled CO and DLCO) in women aged 20 to 49 years between traditional cookstoves (before intervention) and the improved cookstoves with a chimney (after intervention).

3. Assess behaviors, preferences and attitudes that shape improved cookstove adoption and intervention compliance among users of three types of cookstoves; evaluate the reasons for their preferred choice of cookstove; and, assess the potential for sustained maintenance and use of the intervention.

A secondary, health outcome aim is to compare blood pressure in women aged 20 to 49 years between traditional cookstoves (before intervention) and the improved cookstoves with a chimney (after intervention).

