Our study has some potential shortcomings. First, the overall number of participants enrolled in this trial is small. As the trial was designed as a feasibility study spanning three countries with a longitudinal qualitative component, the number of participants able to be enrolled was restricted. However, as designed, the study participants will serve as their own controls and we will be able to evaluate their experiences with a locally constructed, ventilated cookstove and a commercially constructed, ventilated cookstove. Second, we may incur bias in self-reported symptoms after installation of the intervention due to participant awareness of the health benefits associated with improved cookstoves. Another potential limitation of the study is not testing a movement up the fuel ladder to a cleaner fuel, such as liquid-propane gas, biogas or electric cookstoves. However, a cleaner fuel is not an appropriate intervention for our intended populations at this time, as the selected rural populations do not have the supply system or financial ability to sustain an intervention aimed at upward movement on the fuel ladder. Cleaner fuels are the way of the future but to address the burden now, we must focus on appropriate methodologies that utilize currently available energy sources [50].

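### The structured stove-preference item records only a first choice among three stoves; a ranking would let every woman inform each pairwise comparison (optional improvement)

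*Protocol article*

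**What the plan says.** Aim 3, in Study objectives, is broad: "Assess behaviors, preferences and attitudes that shape improved cookstove adoption and intervention compliance among users of three types of cookstoves". It goes on: "evaluate the reasons for their preferred choice of cookstove; and, assess the potential for sustained maintenance and use of the intervention". No single endpoint is named for it.

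The structured item that bears on preference is in Longitudinal behavioral and compliance data: "At the end of the trial, we will ask participants to indicate their preferred cookstove". The noun is singular, and no ranking or paired question is described. The same sentence adds "a final in-depth interview regarding individual preference, experiences using all three cookstove varieties, and the perceived benefits and drawbacks of each stove". Earlier in that section the article says "we will use semi-structured interviewing techniques to assess individual preference and attitudes toward cookstoves", and it also describes monthly counts of meals cooked in total and on the new stove.

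Enrolment is 40 to 46 women per site, 120 to 138 in all (Study setting and populations). The Sample size section says that none was calculated to show an effect on the primary outcomes. The Intervention section says that a commercial and a local stove will be installed and compared in every household, and the Discussion says that "we will be able to evaluate their experiences with a locally constructed, ventilated cookstove and a commercially constructed, ventilated cookstove". No analysis of the preference item is given.

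**The concern.** The design takes every woman through all three stoves, so each can state a full order. The item as described keeps only the top of that order. A woman who names the open fire then says nothing, on this item, about commercial versus local, which is the pair whose sequence is randomised. A woman who names the local stove says nothing about whether she would take the commercial stove over the open fire.

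Both questions matter to a feasibility study meant to inform a larger trial. The Background, under previous research on improved cookstoves, describes the difficulty as two-fold: users must give up the traditional stove and take up the new one. If the pick is later used to compare two stoves, the estimate rests on fewer women than were enrolled. If second choices follow a pattern, it may also differ from the preference of the whole group.

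**Working it through.** **Inputs from the article.** Three stoves; 40 to 46 women per site; three sites. The total reproduces: 3 × 40 = 120 and 3 × 46 = 138. There is no stated test, alpha, preference share or power to reproduce.

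**Assumptions (not in the article).** t, the share whose first choice is the third stove; the split between the two stoves compared; for the power figures, a two-sided exact sign test at 5%.

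**1. Informative women.** Using the pick alone, the expected number is M = N(1 − t). With a full ranking without ties it is N.

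**2. Precision.** The largest 95% half-width of a pairwise share is 1.96 × √(0.25 / M). For N = 120 and t = 50%, M = 120 × 0.5 = 60 and the half-width is 1.96 × √(0.25 / 60) = 0.127.

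**3. Power, as illustration only.** Assumed split 65:35, averaged over M ~ Binomial(N, 1 − t):

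| N | t | Informative women | Half-width (points) | Power |
|---|---|---|---|---|
| 120 | 0 (same as ranking) | 120 | 8.9 | 89.2% |
| 120 | 10% | 108 | 9.4 | 86.5% |
| 120 | 20% | 96 | 10.0 | 82.2% |
| 120 | 1/3 | 80 | 11.0 | 73.9% |
| 120 | 50% | 60 | 12.7 | 60.5% |
| 138 | 0 (same as ranking) | 138 | 8.3 | 94.8% |
| 138 | 20% | 110.4 | 9.3 | 87.3% |
| 138 | 50% | 69 | 11.8 | 67.2% |
| 40 (one site) | 0 (same as ranking) | 40 | 15.5 | 44.1% |
| 40 (one site) | 20% | 32 | 17.3 | 32.3% |
| 40 (one site) | 50% | 20 | 21.9 | 20.0% |

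The half-width is the better guide. At these sizes the exact test moves in steps: at N = 46 it gives 43.3% with a ranking and 43.9% with t = 10%, which is an artefact.

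**4. Tying t to assumed first-choice shares.** Under a Plackett-Luce model for rankings, exact power from the pick against the ranking is:

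- N = 120, commercial/local/traditional 25/40/35, commercial versus local: 78 informative women, 49% against 67%.
- N = 120, shares 25/60/15, commercial versus traditional: 120 × (0.25 + 0.15) = 48 informative women, 36% against 75%.
- The same shares, commercial versus local: 120 × (0.25 + 0.60) = 102 informative women, 98.8% against 99.5%.

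The loss can be large for a less popular stove against the open fire. It is small for commercial versus local when few women choose the open fire.

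**5. Precision or bias?** Under Plackett-Luce the split among women who picked one of the pair equals the split among all women. With shares 25/60/15 it is 25 / (25 + 15) = 62.5% for commercial over traditional either way. So steps 3 and 4 show lost precision only. Bias needs second choices to cluster. Suppose first choices are 60% local, 20% commercial and 20% traditional, and every woman who chose local puts commercial second. Then 60% + 20% = 80% of all women prefer commercial to the open fire, but the pick alone gives 20:20, or 50:50. A larger sample would not correct that. This is a constructed case; the article gives no second-choice pattern.

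**The case against.** The strongest reply is that the item does what Aim 3 asks of it. On choice, the aim says "evaluate the reasons for their preferred choice of cookstove", and a first choice followed by an in-depth interview serves that directly. This stands. A reader might infer that the pick is the endpoint of Aim 3, but the article names no such endpoint, and the aim also covers behaviours, attitudes, compliance and sustained use.

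A reader might also infer that women choosing the third stove are thrown away. That follows only if two stoves are compared on the pick alone, and no such analysis is stated. The share choosing each stove, and any comparison of one stove with the rest, use every respondent. With no sample size calculated for an effect, a loss of power for a test that is not planned is not a defect in the plan. The loss of information about order remains, even for a purely descriptive report.

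Other data help too. In-depth interviews are held every period and cover current and previous stoves. They are led by the participant, but the interviewer probes from a guide. The monthly semi-structured interviews are less open-ended and follow the change from one improved stove to the other. The meal counts give reported use for both improved stoves within each woman. These are relevant, and the counts bear on adoption at least as directly as a stated ranking. But none is stated to produce an order of the three stoves from every woman that can be compared across sites.

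Finally, this is a condensed article without questionnaire wording, so a ranking or follow-up item may exist in the full instrument. That cannot be excluded.

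**Conclusion.** The point holds as an optional improvement. As described, the structured item yields a first choice only, so a comparison of two stoves based on it draws on N(1 − t) women rather than N. For 120 women that is 96 at t = 20% and 60 at t = 50%; for 138 it is about 110 and 69. If nobody chooses the third stove, nothing is lost. The size depends wholly on t, which the article does not give. The power figures depend further on an assumed split, test and ranking model, and illustrate lost precision only.

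The stronger reading, that the preference results would be biased, is not supported by the article or by these power calculations. It would need second choices to cluster, which is possible but not shown. Nothing here is a contradiction or a misstatement in the protocol.

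**What to change.** In Longitudinal behavioral and compliance data, replace the single choice by a ranking, for example: at the final interview, each woman will rank the traditional, the commercially constructed and the locally constructed stove from most to least preferred, with ties allowed. Keep the first choice as a summary; it can be read from the ranking. Report the three pairwise preferences descriptively, by site and by randomised order of the two improved stoves, with ties shown as such. If the full questionnaire already asks for a ranking, it is enough to say so.

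The cost is one or two extra questions at an interview already planned and a small questionnaire change, with no extra visit, staff or participants. The downside is slightly more effort for the respondent and possible ties, mainly between the two lower-ranked stoves. The change has to come before the final interviews, since an order not asked for then cannot be recovered reliably later.

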### Environmental assessment

To assess indoor air quality, we will measure 24-hour indoor air PM and CO concentrations at least once during the baseline period and again during each intervention period. Before the start of every study period, all environmental sampling equipment will undergo quality control checks according to manufacturer instructions to ensure quality performance across all machines. We plan to measure particulate matter with the pDR-1000 (Thermo Scientific, Franklin, MA, USA) passive sampler for a 24-hour period. This device incorporates a pulsed, high output, near-infrared light-emitting diode source. The intensity of the light scattered over the forward angle by particles passing through the sensing chamber is linearly proportional to airborne PM concentration. The pDR-1000 detects particles of 0.3 to 2.0 μm in size more efficiently than 2.0 to 10.0 μm [42-44]; however, there is a high level of agreement between PM determined by the pDR-1000 and gravimetric measurements of PM_2.5_[42,44]. Therefore, PM measured with the pDR-1000 is a good approximation for PM_2.5_. Every machine will be calibrated to zero-air before deployment in the field. We will measure relative humidity (RH) using the HOBO Data Logger (Onset Corp., Bourne, MA, USA) to adjust PM by RH [45]. We will carry out the measurements of ambient CO in the same 24-hour period as the PM measurements with the EasyLog USB CO Monitor (Lascar Electronics, Eerie, PA, USA). We will place the environmental measurement setup approximately 1.0 to 1.5 m above the floor and <1.0 m away from the current cookstove.

### Health outcomes

We will measure height and weight once at baseline for each individual using standard techniques [46]. The following will be measured, beginning at baseline, monthly throughout the trial:

• PEF and FEV_1_: the Piko-1 (nSpire Health, Inc., Longmont, CO, USA) will electronically measure PEF and FEV_1_. We will obtain at least two PEF measurements within 70 L/minute and at least two FEV_1_ measurements within 0.90 L.

• Exhaled CO levels and carboxyhemoglobin (% COHb): a Micro CO (Micro Direct, Inc., Lewiston, ME, USA) will electronically measure exhaled CO (ppm) and % COHb. Any exhaled CO measurement over 10 ppm will be repeated up to three times until two measurements are obtained within ± 2 ppm. The average of the obtained measurements will be reported.

• Pulse oximetry: arterial saturation of oxygen, perfusion index and pulse will be measured by fingertip sensor with a Masimo Rad 5v (Masimo, Irvine, CA, USA).

• Blood pressure: systolic and diastolic blood pressure will be recorded with Omron Healthcare 10 Series (Omron Healthcare, Inc., Lake Forest, IL, USA). The device has an internal calibration check system.

We will measure the following respiratory outcomes at least once at the mid-point of each four month period:

• Spirometry: we will use a flow-based spirometer (EasyOne Pro, ndd Zurich, Switzerland) to measure lung function. We will record forced vital capacity (FVC), FEV_1_, FEV_1_/FVC, PEF and flow-volume curves. We will obtain at least three acceptable and reproducible spirometric maneuvers in accordance with the joint European Respiratory Society and American Thoracic Society guidelines [47]. A field supervisor will review flow-volume curves with technicians on a daily basis to evaluate for quality. De-identified flow-volume curves will be transmitted on a weekly basis to Baltimore for additional over-read and grading. 

• DLCO: this measurement will only be conducted in Peru. We plan to measure DLCO as it is feasible using the EasyOne Pro (ndd, Zurich, Switzerland). We will follow standard criteria from the American Thoracic Society for the measurement of DLCO [48], and adjust values of DLCO for altitude, hemoglobin and COHb levels.

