### Study design

Our study design will be a randomized crossover intervention trial in which all participants will first have a run-in observational period of four months with their traditional cookstove prior to randomization into two intervention arms (Figure 1). At baseline, we will obtain sociodemographic information for each household, respiratory outcomes and other health data for the participating women. Qualitative methods, such as interviews and direct observations, and quantitative questionnaires will be used during the observational period to collect data on fuel use, the cooking process, and the participant’s current perception of their traditional cookstove. One of the intervention arms will first have the commercially constructed, ventilated cookstove installed in their kitchen (Figure 2). They will then be followed for four months. At crossover, we will install a locally constructed, ventilated cookstove and follow the participants for another four months. The other intervention arm will first receive the locally constructed cookstove at the beginning of the first four-month intervention period followed by installation of the commercially constructed improved, ventilated cookstove for the second four-month intervention period. The materials and method of construction of the locally constructed cookstove will vary by site (Figures 3, 4, 5).

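### The 0.90 L repeatability limit for the monthly Piko-1 FEV1 rejects almost no pair of blows, so it does not work as a quality criterion

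*Protocol article*

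**What the plan says.** The protocol article, section Health outcomes, describes two FEV1 measurements.

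- **Monthly, Piko-1.** The list opens with "The following will be measured, beginning at baseline, monthly throughout the trial". Its first item says that "the Piko-1 (nSpire Health, Inc., Longmont, CO, USA) will electronically measure PEF and FEV_1" and sets one criterion: "We will obtain at least two PEF measurements within 70 L/minute and at least two FEV_1_ measurements within 0.90 L". The item gives no acceptability rule, curve review or maximum number of blows, and does not say whether the best or the mean value is kept. The next item, on exhaled CO, does give a repeat limit, a tolerance and an averaging rule.
- **At least once per period, EasyOne Pro.** Here the article asks for "at least three acceptable and reproducible spirometric maneuvers in accordance with the joint European Respiratory Society and American Thoracic Society guidelines", with daily review of curves in the field. In addition, "De-identified flow-volume curves will be transmitted on a weekly basis to Baltimore for additional over-read and grading".

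Under Study objectives, Aim 2 compares respiratory outcomes before and after the improved stoves. It lists spirometry, PEF, exhaled CO and DLCO. Under Study design, "all participants will first have a run-in observational period of four months with their traditional cookstove prior to randomization into two intervention arms", so only the order of the two improved stoves is randomised.

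**The concern.** A repeatability limit is there to make a participant repeat the manoeuvre when two efforts differ too much for both to be maximal. At 0.90 L, blows of 1.8 L and 2.7 L count as agreeing, although one is a third lower than the other. The article thus holds the same quantity to a guideline standard on one device and to almost none on the other.

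Two things are at stake. The first is noise: a feasibility trial meant to inform a larger one should give a credible estimate of FEV1 variability, and poor blows that are let through inflate it. The second is direction. FEV1 depends on effort, the women repeat the manoeuvre monthly, and the traditional-stove period always comes first. If technique improves with practice, the gain runs the same way as a stove benefit in the before-after comparison.

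**Working it through.** The article gives no derivation for 0.90 L and no sample size calculation, so there is no figure of its own to reproduce.

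**Inputs from the article:** limits of 0.90 L (FEV1) and 70 L/min (PEF); monthly measurement; four-month periods with the traditional stove first; 120 to 138 women.

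**Assumptions, not in the article:** FEV1 2 to 3 L; PEF 350 to 450 L/min; within-session blow SD (s) 0.10 to 0.50 L, normal errors.

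**1. Limit relative to the measurement.** 0.90/2.0 = 45%, 0.90/2.5 = 36%, 0.90/3.0 = 30%. For PEF, 70/350 = 20% and 70/450 = 15.6%. Relative to its measurement, the FEV1 limit is about twice as wide.

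**2. How often a pair fails.** The difference of two blows has SD s√2, so P(fail) = 2[1 − Φ(0.90/(s√2))].

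| s (L) | P(fail) at 0.90 L |
|---|---|
| 0.10 | 2 × 10⁻¹⁰ |
| 0.15 | 2 × 10⁻⁵ |
| 0.20 | 0.15% |
| 0.30 | 3.4% |
| 0.40 | 11% |
| 0.50 | 20% |

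The SD must reach 0.90/(1.96 × √2) = 0.32 L before 5% of pairs fail.

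**3. Does it catch a submaximal blow?** Pair one full blow of size M with one at fraction f of M. With d = M(1 − f) and s = 0.10 L, P(accepted) = Φ((0.90 − d)/(s√2)) − Φ((−0.90 − d)/(s√2)). For M = 2.5 to 3.0 L, the pair is accepted 98 to 99.8% of the time at f = 0.8, 50 to 86% at f = 0.7, and 2 to 24% at f = 0.6.

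**4. How much learning the limit lets through.** Simulation with true FEV1 2.6 L and s = 0.10 L. Poor blows are 0.3 to 0.8 L low and make up 30% of early and 10% of later blows. A limit of 0.15 L serves for contrast only; it is not put forward as the guideline's figure.

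| Rule | Spurious rise, 0.90 L | Spurious rise, 0.15 L | Part due to the limit |
|---|---|---|---|
| Mean of two, stop once a pair agrees; two highest must agree | 0.11 L | 0.03 L | 0.08 L |
| Same, but any two may agree | 0.11 L | 0.08 L | 0.03 L |
| Best blow kept, stop once the two highest agree | 0.054 L | 0.025 L | 0.03 L |
| Best blow kept, at least three blows | 0.032 L | 0.019 L | 0.013 L |

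These rows give the whole baseline the early rate. If only the first of about four monthly baseline visits carries it, the shift is about a quarter: 0.107/4 ≈ 0.03 L before any tightening, in the mean-of-two case.

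**5. Scale.** With an assumed SD of change of 0.2 to 0.3 L, the paired change detectable with 80% power is (1.96 + 0.84) × SD/√n. This runs from 2.80 × 0.2/√138 = 0.05 L to 2.80 × 0.3/√120 = 0.08 L.

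**6. Which contrast is affected.** Let technique add b per period. Before-after bias is (b + 2b)/2 = 1.5b. For commercial versus local stove, the two sequences give b − 2b and 2b − b, which average to 0.

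**The case against.** The strongest reply is that the affected measure is secondary and its bias small. Aim 2 names spirometry, which the article assigns to the EasyOne Pro with its own quality control, and does not name the Piko-1 FEV1. The Background offers PEF as the outcome more likely to change quickly. The article asks for at least two agreeing measurements and does not say that testing stops there. The trial has no powered outcome. All of this stands, and it limits the point to one monthly series that should be corrected.

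A reader might infer more, in four ways that the document does not support.

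- **That a spurious gain of about 0.11 L is to be expected.** That figure needs stopping at two blows, keeping their mean, and poor effort throughout the four-month run-in. The article states none of these, and the rates of poor effort are illustrative.
- **That the limit causes the learning bias.** The fixed period order allows it. Two equally submaximal blows pass any limit, so tightening reduces the bias without removing it.
- **That 0.90 L is a decimal slip.** It may be, but nothing in the article settles this.
- **That the 70 L/min PEF limit is also wrong.** The check shows no defect in it. If the same blows had to meet both limits, the PEF limit might even screen out some poor FEV1 efforts, but the text does not say so.

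The reply does not touch the main result. At 0.90 L the criterion rejects almost nothing over a plausible range of SD, and this is a stated rule, not a detail left to a fuller document.

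**Conclusion.** The point holds in a limited form. The 0.90 L limit does not function as a quality criterion for the monthly Piko-1 FEV1: fewer than 0.2% of pairs fail at a blow SD up to 0.20 L, and only SDs of 0.40 to 0.50 L, which are high, bring failures to 11 to 20%. This conclusion rests on the assumed SDs but is not sensitive to them.

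The size of the resulting bias is illustrative. The part due to the limit is about 0.01 to 0.03 L with the best blow kept and 0.03 to 0.08 L with the mean of two kept, and less if poor effort is confined to the first visit. The upper end is comparable with the 0.05 to 0.08 L change that the full sample could detect; the lower end is well below it. The randomised commercial-versus-local comparison is not materially affected, and the EasyOne FEV1 offers an independent check, though it may be taken only once per period. The limit should be corrected; it does not undermine the trial.

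**What to change.** 1. Check 0.90 L against the field manual. Replace it with the FEV1 repeatability limit of the guideline already cited for the EasyOne spirometry, or give a reason for keeping it.
2. Require the two highest blows of the session to meet the limit, set a cap on blows per session, and state that the best value is kept. Which two blows must agree matters: in the mean-of-two case, a tighter limit that any two may satisfy leaves a rise of 0.08 L, against 0.03 L when the two highest must agree.
3. Data collection has begun. Where individual blows were stored, flag earlier sessions that fail the corrected limit and repeat the analysis without them. The article does not say whether single blows are kept, so this may be possible only in part.
4. Treat the EasyOne FEV1 as the lead FEV1 measure and the Piko-1 FEV1 as supportive.

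The cost is one figure and two short rules in the field manual, and about one extra blow per session (from 2.0 to between 2.5 and 3.3 on average in the simulations). Some sessions will be flagged as not repeatable.

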### Sample size

Since this study was designed as a feasibility trial to inform a future, large-scale field trial, we did not calculate a sample size to demonstrate an intervention effect for our primary outcomes. However, the study sample should provide a sufficient indication of the relationship between decreased indoor biomass fuel smoke exposure and improved respiratory health outcomes across and among interventions with improved cookstoves. In addition, the sample size allows for the combination of qualitative and quantitative data collection and monthly respiratory and compliance follow-up.

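### Exhaled CO is re-measured only when it reads above 10 ppm, which biases values near 10 ppm slightly downward and makes precision depend on level; the effect on the stove contrast is small and of unknown direction

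*Protocol article*

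**What the plan says.** The Health outcomes section sets the rule for exhaled CO: "Any exhaled CO measurement over 10 ppm will be repeated up to three times until two measurements are obtained within ± 2 ppm". It continues: "The average of the obtained measurements will be reported". No repeat is stated for a reading of 10 ppm or less. The list that contains exhaled CO opens with "The following will be measured, beginning at baseline, monthly throughout the trial", so the same rule runs through the traditional-stove period and both improved-stove periods.

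The same list treats the hand-held lung function measures differently: "We will obtain at least two PEF measurements within 70 L/minute and at least two FEV_1_ measurements within 0.90 L". That rule has no trigger tied to the level of the reading.

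Under Study objectives, Aim 2 is to "Compare respiratory outcomes (spirometry, PEF, exhaled CO and DLCO) in women aged 20 to 49 years" between the traditional stove (before) and the improved stoves (after). The Background presents exhaled CO as a marker of current exposure.

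**The concern.** The decision to re-measure depends on the outcome's own value. Among readings just above 10 ppm, some are there because the error happened to be positive. Their repeats tend to be lower, and averaging pulls the reported value down. Readings at or below 10 ppm because the error happened to be negative are left alone, so nothing pulls them up. The two kinds of error do not cancel.

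Two things follow. Reported values near the threshold are biased downward, and repeated monthly visits do not average this out because it recurs at every visit. Precision also becomes a function of level, since a low value rests on one reading and a high value on two or more. If the stoves change exhaled CO, the measurement procedure then differs between the conditions that Aim 2 compares.

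Separately, the sentence on averaging can mean all readings taken or only the two that agree, and three sites could apply it differently.

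**Working it through.** **Inputs.** From the protocol: the 10 ppm trigger, up to three repeats, the 2 ppm agreement limit, and reporting of an average. The protocol states no figure to reproduce. It gives no exhaled CO level for any stove and no reading error, so these are assumed: normal reading error with mean zero and SD 1, 2 or 3 ppm; true levels lognormal with geometric SD 1.7; traditional/improved medians from 6/4 to 25/12 ppm.

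**Step 1: one repeat, by formula.** Let the true level be T and the readings X1 = T + e1 and X2 = T + e2. The reported error is e1 when X1 is 10 or less, and (e1 + e2)/2 when X1 exceeds 10. Hence

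bias = -0.5 × E[e1 × 1(X1 > 10)] = -0.5 × SD × φ((10 - T)/SD),

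where φ is the standard normal density. This is never positive. It is largest in size at T = 10, where φ(0) = 0.399 and the bias is -0.5 × 0.399 × SD = -0.20 SD. That is -0.20, -0.40 and -0.60 ppm for SD 1, 2 and 3.

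**Step 2: the full rule, by simulation** (1,000,000 draws per setting; up to three repeats, stopping once two readings lie within 2 ppm; if none agree, all four are averaged).

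- At T = 10, averaging all readings: about -0.20, -0.44 and -0.7 ppm for SD 1, 2 and 3. Averaging only the agreeing pair gives slightly larger values (-0.21, -0.48 and -0.78).
- With SD 2, averaging all readings: -0.07 at T = 6, -0.29 at 8, -0.44 at 10, -0.29 at 12, about -0.02 at 15 and 0.00 at 20.

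The bias sits around the threshold and fades on both sides.

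**Step 3: precision.** A single reading has error SD equal to the reading SD. The mean of two has SD/√2 = 0.71 SD.

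**Step 4: the stove contrast.** The true mean difference is (difference in medians) × exp((ln 1.7)²/2) = (difference in medians) × 1.15. Results below average all readings.

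| Medians, traditional/improved (ppm) | True difference (ppm) | Change in contrast, SD 1 | SD 2 | SD 3 |
|---|---|---|---|---|
| 6/4 | 2.30 | -0.6% | -2.9% | -5.5% |
| 8/5 | 3.45 | -0.5% | -2.1% | -3.3% |
| 12/8 | 4.60 | 0.0% | +0.2% | +0.8% |
| 20/10 | 11.5 | +0.2% | +0.9% | +1.9% |
| 25/12 | 15.0 | +0.2% | +0.8% | +1.7% |

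Averaging only the agreeing pair widens the extremes to -0.138/2.30 = -6.0% (medians 6/4, SD 3) and about +2% (medians 20/10, SD 3: 0.241/11.5 = +2.1%). If simulated readings are also cut off at zero, the 6/4, SD 3 case reaches about -10%. The extra comes from the cut-off, which distorts low readings under any repeat rule, so it is not counted here.

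**Step 5: why the sign changes.** With medians 20/10 and SD 2, 90% of first readings on the traditional stove exceed 10 ppm, against 51% on the improved stoves. Yet the mean bias is -0.07 ppm on the traditional stove and -0.17 ppm on the improved ones. What counts is how many true levels lie near 10 ppm, not how many readings exceed it.

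**The case against.** **Size.** The larger figures need a reading SD of 2 or 3 ppm. Two readings agree within 2 ppm with probability 2Φ(2/(SD√2)) - 1, which is 84%, 52% and 36% for SD 1, 2 and 3. If the limit was chosen so that it can usually be met, which is an inference, SD 1 is the most plausible and the contrast moves by less than 1%. The trial is also a feasibility study: "we did not calculate a sample size to demonstrate an intervention effect for our primary outcomes". This stands and is why the point is minor. It does not make the rule unbiased.

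**Direction.** A reader might infer that high readings, and so the bias, occur mostly on the traditional stove, and that the stove effect must therefore shrink. The protocol does not support this. More repeats in that period is plausible, but a woman truly far above 10 ppm is re-measured without bias. The contrast shrinks if traditional-stove levels are mostly at or below about 10 ppm, and grows slightly if they are well above it while improved-stove levels fall near it. No levels are given that would settle which applies.

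**Which readings are averaged.** It would also go too far to say that the discordant readings are included. The wording permits that, and equally permits the agreeing pair alone. The downward bias appears either way.

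**Missing detail.** An article condenses its full protocol. But the trigger is a stated rule that produces biased values, not something left out.

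**Remedy.** Changing the rule now could itself create a difference between periods, because data collection has begun at all sites and the traditional-stove period always comes first. This stands and shapes the fix.

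**Conclusion.** The one-sided repeat rule is a real but minor flaw. Given reading error with mean zero, reported exhaled CO for women truly near 10 ppm is too low by about 0.2 reading SDs or slightly more, which is about 0.2 to 0.7 ppm for an assumed SD of 1 to 3 ppm. Well away from 10 ppm it is unbiased. Precision depends on level whatever the size of the error.

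For the traditional-versus-improved contrast, the change is roughly -6% to +2% across the assumed scenarios and within 1% at SD 1. Its direction cannot be determined from the protocol. The bias at the threshold follows from the rule and the mean-zero error; the percentages rest entirely on the assumed levels, spread and reading SD.

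**What to change.** - Make the number of readings independent of their level. For example, take two at every visit and a third if the first two differ by more than 2 ppm. A third reading then depends on disagreement, not on being high, and symmetric error leaves no selection bias.
- State whether all readings or only the agreeing pair are averaged, and use that at all three sites.
- Do not mix rules across periods. Where first readings were recorded separately, which the protocol does not say, analyse the first reading at every visit in all three periods, as the main or a sensitivity analysis, and keep the repeats for quality control. Where only averages were kept, describe the rule as a limitation and report how many visits in each period triggered it, if that is known.

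Cost: one extra breath at visits reading 10 ppm or below under the uniform rule, or slightly more noise at high values under the first-reading analysis.
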